## Abstract

**Background:**

In an effort to reduce the risk of breast cancer-related arm lymphedema, patients are commonly advised to avoid heavy lifting, impacting activities of daily living and resistance exercise prescription. This advice lacks evidence, with no prospective studies investigating arm volume changes after resistance exercise with heavy loads in this population. The purpose of this study is to determine acute changes in arm volume after a session of low- and heavy-load resistance exercise among women undergoing adjuvant chemotherapy for breast cancer at risk for arm lymphedema.

**Methods/Design:**

This is a randomized cross-over trial. *Participants*: Women receiving adjuvant chemotherapy for breast cancer who have undergone axillary lymph node dissection will be recruited from rehabilitation centers in the Copenhagen area. *Intervention:* Participants will be randomly assigned to engage in a low- (two sets of 15–20 repetition maximum) and heavy-load (three sets of 5–8 repetition maximum) upper-extremity resistance exercise session with a one week wash-out period between sessions. *Outcome:* Changes in extracellular fluid (L-Dex score) and arm volume (ml) will be assessed using bioimpedance spectroscopy and dual-energy x-ray absorptiometry, respectively. Symptom severity related to arm lymphedema will be determined using a visual analogue scale (heaviness, swelling, pain, tightness). Measurements will be taken immediately pre- and post-exercise, and 24- and 72-hours post-exercise. *Sample size:* A sample size of 20 participants was calculated based on changes in L-Dex scores between baseline and 72-hours post exercise sessions.

**Discussion:**

Findings from this study are relevant for exercise prescription guidelines, as well as recommendations regarding participating in activities of daily living for women following surgery for breast cancer and who may be at risk of developing arm lymphedema.

**Trial registration:**

Current Controlled Trials ISRCTN97332727. Registered 12 February 2015.

**Electronic supplementary material:**

The online version of this article (doi:10.1186/s12885-016-2548-y) contains supplementary material, which is available to authorized users.

## Background

Approximately 20 % of breast cancer survivors develop breast cancer-related arm lymphedema BCRL [1], with an estimated 80 % of cases presenting within the first two years of diagnosis [2]. It is associated with significant impairments in gross and fine motor skills affecting work, home and personal care functions, as well as recreational and social relationships [3, 4]. While the etiology of BCRL is unknown [1, 5], findings from a systematic review and meta-analysis from 2013 [1] including 72 studies demonstrate that axillary lymph node dissection, more extensive breast surgery, radiotherapy, chemotherapy, being overweight or obese and physical inactivity are consistently associated with increased BCRL risk [1].

Participation in resistance exercise has been found to be a safe and effective exercise modality among breast cancer survivors at risk of BCRL [6, 7], and is associated with increases in lean muscle mass and strength, which in turn positively effect physical function and ability. Furthermore, findings from a recent meta-analysis [6] suggest that resistance exercise can reduce the risk of BCRL versus control conditions (OR = 0.53 (95 % CI 0.31–0.91); I^2^ = 0 %). However, the current evidence-base is derived from studies that have evaluated resistance exercise intensities considered to be low to moderately heavy (60–80 % of 1 repetition maximum (RM) or 8–15 RM) [6, 7]. Yet, exercise science literature indicates that heavy-load resistance exercise (80–90 % 1RM or 5–8 RM) [8] is more effective than low- to moderate-load resistance exercise in generating muscle strength gains [9]. There is therefore a clear need for studies evaluating the safety of heavy-load resistance exercise in the at-risk population [7].

In a novel study by Cormie et al. [10], which evaluated the effect of low- and heavy-load resistance exercise among a sample with BCRL, lymphedema status and lymphedema symptoms remained stable immediately after exercise, and 24- and 72-hours after exercise, irrespective of load. While these findings provide important information for women with BCRL, the purpose of this study is to determine acute changes in extracellular fluid, arm volume and associated lymphedema symptoms after a session of low- and heavy-load resistance exercise in women at risk for BCRL. It is hypothesized that no interlimb differences in extracellular fluid, arm volume or lymphedema-associated symptom severity will be observed over time or between resistance exercise loads.

## Design

This study is a randomized, cross-over trial (Table 1 here).

**Table 1 Tab1:** Trial registration data

Trial registration data	
Primary registry and trial identify number	Current Controlled Trials ISRCTN97332727.
Date of registration in primary registry	12 February 2015.
Secondary identifying numbers	H-3-2014-147, 30-1430
Source of monetary or material support	University Hospitals Centre for Health Research, Copenhagen University Hospital Rigshospitalet
Primary sponsor	University Hospitals Centre for Health Research, Copenhagen University Hospital Rigshospitalet
Secondary sponsor	
Contact for public queries	KB, MHS, PhD-stud. [contact], [name], [name]
Contract for scientific queries	KB, MHS, PhD-stud. [contact], [name], [name]
Public title	A trial to detect differences in arm volume after low- and heavy-load resistance exercise among patients receiving adjuvant chemotherapy for breast cancer at risk for arm lymphedema: Study Protocol
Scientific title	A randomized cross-over trial to detect differences in arm volume after low- and heavy-load resistance exercise among patients receiving adjuvant chemotherapy for breast cancer at risk for arm lymphedema: Study Protocol
Countries of recruitment	Denmark
Health condition or problem studied	Breast cancer-related arm lymphedema
Intervention	Heavy vs low load resistance exercise for the upper extremities
Key inclusion and exclusion criteria	Inclusion criteria: > 18 years of age, unilateral breast surgery, axillary node dissection, undergoing adjuvant chemotherapy for breast cancer
	Exclusion criteria: Previously treated for breast cancer, diagnosis of BCRL and/or currently receiving treatment for BCRL, or having conditions hampering resistance exercise of the upper body, or having participated in regular upper-body heavy resistance exercise during the last month
Study type	Interventional
	Randomized cross-over, assessor blinded
	Safety
Date of first enrolment	31-03-2015
Target sample size	40
Recruitment status	Recruiting
Primary outcome	Arm extracellular fluid (L-dex score) post-, 24- and 72 h post exercise
Key secondary outcomes	Arm volume (ml) post-, 24- and 72 h post exercise

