## Methods

### Participants / Recruitment

Twenty women allocated to adjuvant chemotherapy for breast cancer consisting of three cycles of 3-weekly epirubicin followed by three cyles of 3-weekly docetaxel will be recruited from municipality lead rehabilitation centers in the Copenhagen area and from a waiting list to the *Body and Cancer* program [11, 12], at the University Hospitals Center for Health Research (UCSF) at the Copenhagen University Hospital, Rigshospitalet. All patients will be screened for inclusion by health professionals (nurse or physical therapist) at the respective centers. Potential participants fulfilling inclusion criteria; over 18 years of age, unilateral breast surgery, axillary node dissection, and initiating /undergoing adjuvant chemotherapy for breast cancer (stage I - III) will be contacted during their first three cycles of chemotherapy (Fig. 1). Patients previously treated for breast cancer, with a diagnosis of BCRL and/or currently receiving treatment for lymphedema, or having conditions hampering resistance exercise of the upper body, or having participated in regular (>1 × / week) upper-body heavy resistance exercise during the last month will be excluded.

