### Sample size and analytical plan

The sample size calculation is based on changes in L-Dex scores between baseline and 72 h post-resistance exercise sessions. From results of Cormie et al. [10] we hypothesize the standard deviation in the distribution to be 1.9 units. No published normative change scores exist for the at-risk population, as well as no evidence regarding a threshold for a clinically significant acute change. For patients with BCRL a change score of 2L-Dex units is considered clinically relevant based on clinical experience. We believe that an L-Dex of 2 units is too conservative in the at-risk population, and have therefore set a threshold at 3L-Dex units. Thus, if there is no difference between groups, then 18 patients are required to be 90 % sure that the limits of a two-sided 90 % confidence interval will exclude a difference in means of more than 3.0. To allow for possible drop-outs we plan to include 20 patients.

Data will be analyzed using the Statistical Package for Social Sciences (SPSS) software (version 19) for Windows (IBM SPSS, Chicago, IL). Analysis will include standard descriptive statistics and both intention to treat and per-protocol analysis will be performed. Using a generalized estimating equations framework for continuous outcomes to determine time (baseline, pre-, post, 24- and 72 h) and intervention (low-/ heavy-load) effects, the interaction between time and intervention will be considered [23]. Two-tailed *p* < 0.05 will be taken as evidence of statistical significance.

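### Table 1 gives a target sample size of 40, while the Abstract, Recruitment section and sample-size section plan 20, and the article does not explain the difference

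*Protocol article*

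**What the plan says.** The protocol article states the planned number in four places.

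- **Design, Table 1 (Trial registration data):** "Target sample size 40". The same table shows the trial as recruiting, with first enrolment on 31-03-2015.
- **Abstract, Methods/Design:** "A sample size of 20 participants was calculated based on changes in L-Dex scores".
- **Participants / Recruitment:** "Twenty women allocated to adjuvant chemotherapy for breast cancer" are to be recruited.
- **Sample size and analytical plan:** "18 patients are required to be 90 % sure that the limits of a two-sided 90 % confidence interval" lie inside a margin of 3.0 L-Dex units. The section then adds the drop-out allowance: "To allow for possible drop-outs we plan to include 20 patients".

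The calculation also rests on "we hypothesize the standard deviation in the distribution to be 1.9 units" and on the condition "if there is no difference between groups". The same paragraph mentions a 2-unit threshold used for patients who already have lymphedema, judges it too strict for the at-risk population, and adopts 3 units.

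The design is a cross-over, so each woman completes both the low-load and the heavy-load session.

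**The concern.** The target sample size tells a reader how many women the trial set out to enrol, and it is the yardstick for judging whether recruitment was completed. Here one article gives two values that differ by a factor of two. No footnote, amendment note or definition explains the larger one.

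The table row is a sample size, and in a cross-over 20 women are 20 participants, not 40. If the 40 counts sessions, the entry is wrong as labelled. If it is a target registered before the design was settled, the target was halved and the article does not say so. In a trial meant to show that heavy loading makes no important difference, a halved target matters most if it came from a wider margin, because the margin defines what the trial can claim. A reader cannot tell which explanation applies.

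**Working it through.** **Inputs, all from Sample size and analytical plan:** SD 1.9; margin 3.0; true difference 0; 90% power; two-sided 90% confidence interval, i.e. 5% in each tail.

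**1. Reproducing the stated 18.** For equivalence of two means with true difference zero, the type II error of 0.10 is split over the two limits. Both normal quantiles are then z(0.95) = 1.645, with sum 3.290.

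n per group = 2 × (SD × 3.290 / margin)²
= 2 × (1.9 × 3.290 / 3.0)² = 8.68, rounded up to 9.

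Total = 2 × 9 = 18, the stated figure.

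**2. From 18 to 20.** 18 / 0.90 = 20. The 10% drop-out rate is implied by 18/20; the protocol does not state it.

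**3. Can the same inputs give 40?** No. To go from 18 required to 40 recruited, the allowance would have to be 1 − 18/40 = 55%, which appears nowhere.

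**4. Where 40 could come from.**
- Margin of 2 units in the same formula: 2 × (1.9 × 3.290 / 2)² = 19.5, i.e. 20 per group and 40 in total, with no drop-out allowance.
- Counting sessions: 20 women × 2 sessions = 40.

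Both reproduce the number. The document supports neither as the actual origin.

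**5. What the difference means for precision.** The expected half-width of the 90% interval for the mean within-woman difference is about t(0.95, n − 1) × SD_d / √n, with t = 1.729 for n = 20 and 1.685 for n = 40. The protocol does not say whether 1.9 is the SD within each condition or the SD of the difference, and it gives no within-patient correlation. SD_d is therefore an assumption, shown here over a range.

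| Assumption | SD_d | n = 20 | n = 40 |
|---|---|---|---|
| 1.9 per condition, correlation 0 | 1.9 × √2 = 2.69 | 1.04 | 0.72 |
| 1.9 per condition with correlation 0.5, or 1.9 is already the SD of the difference | 1.9 | 0.73 | 0.51 |

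The ratio does not depend on SD_d: (1.729 / 1.685) × √(40/20) = about 1.45.

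**6. Against the margin.** With a true difference of zero and the larger SD_d of 2.69, the normal-approximation probability that the 90% interval lies within ±3.0 is 0.999 with 20 women. With 40 it is indistinguishable from 1.

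**The case against.** The strongest defence is that the protocol is not really in doubt about its own size. All three places that set the design say 20, and only 20 comes with a calculation. The 40 appears once, in a table that reports registry fields. A reader asking how many women this protocol plans to enrol gets one justified answer. That stands. A reader might infer that stopping at 20, at 40 or anywhere between could each be defended later, but the design text does not support this.

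Three further inferences also go beyond the document.

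- **That the public registry holds 40, so a trial ending at 20 would have missed half its registered target.** The registry record is not at hand. The 40 may be a faithful copy of it or an error in the table.
- **That the margin was relaxed from 2 to 3 units after registration and the target halved.** The arithmetic fits. However, it gives 40 before any drop-out allowance, and the session count fits equally well. The article reports no change.
- **That the trial would be underpowered at 20.** Step 6 shows otherwise under the planning assumptions.

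The defence does not remove the conflict. Table 1 is not a change log and does not mark the 40 as superseded. Nor is this a detail left to a fuller protocol: two stated values disagree. If the registry does hold 40, the disagreement is public and unexplained. If it does not, the table is wrong.

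**Conclusion.** The inconsistency is real: 40 in Table 1 against 20 in three other places, without explanation. The document's own inputs reproduce 18 and support 20; they do not give 40. The error is one of consistency, since the sample-size arithmetic itself reproduces.

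The statistical consequence is modest. The 90% interval is about 1.45 times as wide at 20 as at 40 whatever the SD. In absolute terms that is 1.04 against 0.72 L-Dex units, or 0.73 against 0.51, depending on an assumption the protocol leaves open. Both sizes should exclude the 3.0 margin if the true difference is zero. What suffers is the clarity of the recorded target and, if the target was changed, the disclosure of that change. It should be corrected, but it does not threaten the primary comparison.

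**What to change.** State one target wherever the number appears. On the protocol's own calculation it is 20 women, each completing both sessions, and the Table 1 entry should be corrected to match.

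The sponsor should first establish where the 40 came from, so that a genuine change is not simply overwritten:

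- **If 40 is a table error or a session count:** correct the cell. Nothing else changes.
- **If the registry holds 40:** update the record and disclose when and why the target changed, including whether a change of margin from 2 to 3 units was the reason.
- **If 40 is the true target:** redo the sample-size paragraph with inputs that lead to it, and correct the Abstract and the Recruitment section.

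In the first two cases the cost is one table cell, a registry check and at most a sentence or two of explanation. The third requires a revised calculation.

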## Methods

### Participants / Recruitment

Twenty women allocated to adjuvant chemotherapy for breast cancer consisting of three cycles of 3-weekly epirubicin followed by three cyles of 3-weekly docetaxel will be recruited from municipality lead rehabilitation centers in the Copenhagen area and from a waiting list to the *Body and Cancer* program [11, 12], at the University Hospitals Center for Health Research (UCSF) at the Copenhagen University Hospital, Rigshospitalet. All patients will be screened for inclusion by health professionals (nurse or physical therapist) at the respective centers. Potential participants fulfilling inclusion criteria; over 18 years of age, unilateral breast surgery, axillary node dissection, and initiating /undergoing adjuvant chemotherapy for breast cancer (stage I - III) will be contacted during their first three cycles of chemotherapy (Fig. 1). Patients previously treated for breast cancer, with a diagnosis of BCRL and/or currently receiving treatment for lymphedema, or having conditions hampering resistance exercise of the upper body, or having participated in regular (>1 × / week) upper-body heavy resistance exercise during the last month will be excluded.

**Fig. 1 Fig1:**
[figure not shown]
Study time line

Those fulfilling study criteria and expressing interest in study participation will thereafter be screened for BCRL by the first author after the third cycle of chemotherapy, using bioimpedance spectroscopy (BIS). Furthermore, in accordance with common toxicity criteria (CTC) v3.0 lymphedema criteria for the limb [13], patients will be visually inspected to detect differences in signs of swelling between arms. Those presenting with BCRL, defined as a lymphedema index (L-Dex) score of 10 or greater [14–16] (as assessed by BIS), and/or visual signs of swelling (obscuration of anatomic architecture or pitting edema) of the at-risk arm [13] will be referred for treatment, and will not be included in the study.

Written and oral information regarding the study will be delivered by the first author, as well as obtainment of informed written consent.

### Concealed randomization

Prior to the study, a computer-generated random sequence will be generated by an external researcher not otherwise affiliated with the study, and concealed in opaque envelopes. Group assignment will be disclosed to the first author by telephone after study inclusion and participation in the familiarization period. Participants will be allocated using a 1:1 ratio to partake in either low- or heavy-load resistance exercise first.

### Exercise sessions

Participants will engage in a familiarization period, comprising of two training sessions up to one week apart, after the third cycle of chemotherapy. Each session will start with a 10- minute aerobic warm-up using a cross-trainer (Glidex, Technogym®, Gamettola, Italy). During the first familiarization session participants will be introduced to four upper-body exercises (chest press, latissimus pull down, triceps extension (Technogym®, Gamettola, Italy) and biceps curl (free weights)) followed by a 1RM strength test in each exercise. At the second familiarization session, two sets of 10–15 RM will be performed and a new 1RM strength test will be undertaken to ensure accuracy of subsequent exercise prescription. Participants will engage in the first experimental session after the first cycle of docetaxel (fourth chemotherapy), followed by a wash-out period of 6 days. Two sets of 15–20 RM of each exercise will be performed during low-load resistance exercise and three sets of 5–8 RM during heavy-load. All sets will be performed to muscle fatigue in sessions individually supervised by the first author (a physical therapist with experience in exercise prescription for women with breast cancer) at training facilities located at Rigshospitalet.

### Outcomes (pre- and post, 24- and 72-hours after resistance exercise)

Measurements will be performed by medical technicians with no knowledge of group (low- / high-load first) allocation at the Department of Clinical Physiology and Nuclear Medicine at the Copenhagen University Hospital, Rigshospitalet. Participants are advised to maintain their normal activities during study participation. At all assessment points, participants will be asked about their physical activities, and any extraordinary activities will be recorded.

#### Primary outcome

*Extracellular fluid* BIS (SFB7, Impedimed, Brisbane, Australia) directly measures the impedance of extracellular fluid and has a high reliability for detecting BCRL [14, 16, 17] (intraclass correlation coefficient (ICC) = 0,99) [18]. Participants will be positioned in supine with arms and legs slightly abducted from the trunk with palms facing down. Utilizing the principle of equipotentials, four single tab electrodes will be placed in a tetrapolar arrangement [17]. Measurement electrodes will be placed on the dorsum of the wrist midway between the styloid processes, with current drive electrodes placed five centimeters distally on the dorsal side over the third metacarpal of the hand, and approximately midway on the third metatarsal on the dorsum of the foot [17, 19]. Each limb will be measured at a range of frequencies using the manufacturer’s software. The ratio of impedance between the at-risk and non-affected limb will be calculated and converted into a L-Dex score.

#### Secondary outcomes

*Arm volume* Dual energy x-ray absorptiometry (DXA) (Lunar Prodigy Advanced Scanner, GE Healthcare, Madison, WI) measures tissue composition using a three-compartment model that is sensitive to changes in upper-limb tissue composition [20, 21]. Using previously derived densities for: fat (0.9 g/ml); lean mass (1.1 g/ml); bone mineral content (BMC) (1.85 g/ml), the measured DXA tissue weights will be transformed into estimated arm volumes [20, 21].

Participants will be positioned on the scan-table, lying supine with the arm separated from the trunk. If necessary a Velcro band will be used over the breast to ensure space between the arm and truncus. Each arm will be scanned separately. Small animal software (Encore version 14.10) will be used to analyze the scans as described by Gjorup et al. [20]. Scans will be point typed where soft tissue is marked as bone, whereafter regions of interest (ROIs) will be drawn around the hand and the arm on every scan (Fig. 2). All scans will be analyzed by one examiner (last author) with experience in analyzing DXA scans.

**Fig. 2 Fig2:**
[figure not shown]
DXA regions of interest

*Subjective assessment of symptoms* The severity of symptoms related to arm lymphedema including swelling, heaviness, pain and tightness, will be monitored using a visual analogue scale, whereby 0 represents no discomfort and 10 is indicative of very severe discomfort [10].

